### Statistical analysis

All RCT analyses take place after the 12 months follow-up and no intermediate analyses are performed. Publication of the results from the trial will take place after the two-year follow-up. Between-group comparison is analysed on an intention-to-treat basis. Comparison of the primary dichotomous outcome is analysed through logistic regression for repeated measurement coded as "recovered" or "not recovered". Logistic regression is adjusted for baseline values and prognostic factors such as gender and duration of symptoms. These adjustments are only included in the final model if the estimate changes more than 10% when entering the variables in the model. Secondary analysis includes a per-protocol analysis and a predefined subgroup analysis investigating the interaction between treatment and compliance.

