## Methods

### Design

The study involves a single blind pragmatic cluster randomised controlled trial. The protocol conforms to CONSORT guidelines for non-pharmacological interventions [17] and is approved by the local ethics committee in North Denmark Region (N-20110020). All students below 18 years of age are required to give informed together with parental consent. Students aged 18 or 19 are allowed to give informed consent without parental consent.

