### Patient selection

Four upper secondary schools were invited to participate in the study. All four schools accepted the invitation. All students (approximately 2500), aged 15-19 years, in the schools are invited to answer an online questionnaire as part of their physical education lessons. The students who report knee pain are contacted by telephone and offered a clinical examination by an experienced rheumatologist who evaluates which students are eligible to enter the study (Figure 1).

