### Randomisation

Subjects who fit the inclusion criteria are offered to participate in the study. After all subjects have undergone a clinical examination and signed an informed consent, students are cluster-randomised into two intervention groups based on which school they attend. Cluster randomisation is chosen to minimise the bias that could be introduced if more than one student in each class is diagnosed with PFPS, but randomised to different treatment groups.

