### Information and education

One physiotherapist will carry out all patient education in the two clusters that are randomised to patient education only. The physiotherapist has previous experience in treating adolescents and PFPS and has more than two years of practical experience. The information and education is standardised and covers the topics of: why does it hurt: pain management; information on how to modify physical activity; how to return slowly to sports; how to cope with knee pain, and information on how to increase knee alignment during sit-to-stand, standing, walking, stair walking and bicycling. The patients will also receive this information in an eight-page leaflet. This session is expected to take approximately 30 minutes depending on the number of questions from the student or the parents.

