### Information and education plus multimodal physiotherapy

The multimodal physiotherapy is carried out by two physiotherapists (one in each of the two clusters). Both have previous experience in treating adolescents and subjects with PFPS, and have more than two years of practical experience. The multimodal physiotherapy consists of patellofemoral soft tissue mobilisation, stretching of the muscles around the hip and knee, patellar taping, neuromuscular training of the muscles around the foot, knee and hip, quadriceps strength training for the knee and hip and instructions on home exercises [12,20]. The intervention is carried out on the school premises three times per week immediately after the end of class for a total of three months. Students are expected to vary greatly with regard to pain severity and level of function. To tailor the exercise therapy to the specific performance level of the student, all exercises are available in three or four different levels to enable progression (see Table 1). All students start with exercises at level one. Three general rules have been made to determine when progression of the exercises will occur:

**Table 1 T1:** the exact exercise, number of repetitions and external load will be determined by the physiotherapist.

Functional retraining exercises performed three times a week	•Sitting (isometric) • Sit-to-stand • Single step up • Stair walking • Single leg squat

Quadriceps muscle strengthening performed three times/week	• Inner range (open kinetic chain) • Mid range (open kinetic chain) • Weight-bearing

Hip abduction strengthening performed three times a week	• Side-lying hip abduction • Side-lying hip abduction with rubber band for resistance • Standing, hip abduction of the non-weight bearing leg • Standing, hip abduction of the non-weight bearing leg with rubber band between the ankles as extra resistance • Side-lying bridge • Side-bridge with hip abduction

Stretching	• Hamstring muscle stretches in sitting • Anterior hip structures stretch. Subjects in prone position, one hip externally rotated and with both the hip and knee flexed • Patellofemoral joint mobilisation and soft-tissue will be performed by the physiotherapist and taught so patient can perform this themselves

Patellar taping	• Combination of tilt, medial glide and fat pad unloading as necessary- the tape will be applied by the physiotherapist each training session

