### Outcome measurements

#### Self-reported outcome measurements

Self-reported questionnaires are filled out by the students with PFPS at baseline, 3, 6, 12 and 24 months after inclusion in the study. A physiotherapist not involved in the treatment, will hand out all questionnaires during follow-up and answer questions from the students. The primary outcome measure is perception of recovery after 12 months measured on a 7-point Likert scale ranging from "completely recovered" to "worse than ever". Students are categorised as "recovered" if they rate themselves as **"**fully recovered**" **or **"**strongly recovered**"**. Students rating themselves in one of the other five categories from **"**slightly recovered**" **to **"**worse than ever" are categorised as "not recovered" [11]. Secondary outcomes include Knee Injury and Osteoarthritis Outcome Score (KOOS) [22]. The change from baseline to each point of follow-up in the average score of the five KOOS subscale scores (KOOS_5_) covering pain, symptoms, activities of daily living, difficulty in sports and recreational activities, and quality of life are used. Further, EQ5D is used as s self-reported generic measure of health status [23].

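### The primary logistic regression names no term for school, the randomised unit; with any between-school correlation its standard errors are too small and its type I error exceeds 5%

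*Protocol article*

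**What the plan says.** Under Design: "The study involves a single blind pragmatic cluster randomised controlled trial". Under Patient selection, four schools were approached and "All four schools accepted the invitation". Under Randomisation, "students are cluster-randomised into two intervention groups based on which school they attend".

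The intervention sections show two schools in each arm, with different delivery:

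- Education only: "One physiotherapist will carry out all patient education in the two clusters that are randomised to patient education only". The education is one-to-one.
- Education plus physiotherapy: "The multimodal physiotherapy is carried out by two physiotherapists (one in each of the two clusters"). Supervised group sessions take place at the school three times a week for three months.

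Under Self-reported outcome measurements, "The primary outcome measure is perception of recovery after 12 months measured on a 7-point Likert scale", then split into recovered and not recovered. Questionnaires are completed at baseline, 3, 6, 12 and 24 months.

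Under Statistical analysis, "Comparison of the primary dichotomous outcome is analysed through logistic regression for repeated measurement". It continues: "Logistic regression is adjusted for baseline values and prognostic factors such as gender and duration of symptoms". A covariate is retained only if it moves the estimate by more than 10%. Neither this section nor any other names a school effect, a variance clustered on school or a school-level analysis.

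Under Sample size, the article expects 20% versus 50% recovery and gives 51 per group for power 0.90 and alpha 0.05, raised to 56 for 10% drop-out. No ICC or design effect appears.

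**The concern.** In a cluster randomised trial, chance variation between the randomised units is part of the error of the treatment comparison. Here that comparison sets two schools against two schools. Repeated measurement, read against the visit schedule, means several visits of one student. It says nothing about two students of the same school being more alike than two students of different schools. A model that handles only the first kind of dependence treats roughly 100 students as independent when four units were allocated.

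The covariate rule does not bring school in. A change-in-estimate criterion concerns confounding of the estimate, not its variance. Nor can a full set of school indicators sit beside treatment, because schools are nested in arm and the indicators would be collinear with it.

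The design gives reasons to expect some correlation. In the active arm, students train together at school under a physiotherapist who differs between the two schools and who sets exercise, repetitions and load. In the education arm, one physiotherapist serves both schools, so therapist adds no between-school variance there, but therapist is fully confounded with arm. At stake are the p-value and confidence interval of the single primary claim.

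**Working it through.** **Step 1: reproduce the stated sample size.** Inputs from Sample size: 0.20 versus 0.50, power 0.90, alpha 0.05 (taken as two-sided; the article does not say).

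- Arcsine formula: 2(1.960 + 1.282)² / (2·asin√0.5 − 2·asin√0.2)² = 50.7, so 51 per group.
- Pooled normal formula: [1.960·√(2·0.35·0.65) + 1.282·√(0.16 + 0.25)]² / 0.30² = 51.01, which rounds up to 52. Power at 51 is 0.900.

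The stated 51 is therefore the figure for individual randomisation, with a design effect of 1.

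**Step 2: type I error when school is ignored.** With m students per school, the design effect is DE = 1 + (m − 1)·ICC. The true standard error is √DE times the one the model reports, so a nominal two-sided 5% test rejects with probability 2[1 − Φ(1.96/√DE)]. The value of m is 25.5 (51 evaluable per group over two schools) or 28 (56 enrolled per group). The ICC values are assumptions.

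| ICC (assumed) | DE, m = 25.5 | √DE | Type I error | DE, m = 28 | √DE | Type I error |
|---|---|---|---|---|---|---|
| 0 | 1.000 | 1.00 | 5.0% | 1.000 | 1.00 | 5.0% |
| 0.005 | 1.123 | 1.06 | 6.4% | 1.135 | 1.07 | 6.6% |
| 0.01 | 1.245 | 1.12 | 7.9% | 1.270 | 1.13 | 8.2% |
| 0.02 | 1.490 | 1.22 | 10.8% | 1.540 | 1.24 | 11.4% |
| 0.05 | 2.225 | 1.49 | 18.9% | 2.350 | 1.53 | 20.1% |
| 0.10 | 3.450 | 1.86 | 29.1% | 3.700 | 1.92 | 30.8% |

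**Step 3: check by simulation.** Beta-binomial data were simulated for four schools of 26, two per arm, with equal recovery of 20%, 35% or 50% in both arms (200,000 runs each) and an unadjusted logistic Wald test at 12 months. It rejects in 4.4-5.1% of runs at ICC 0, 7-8% at 0.01, 10-11% at 0.02, 18-20% at 0.05 and 28-31% at 0.10. A school-level t test on 2 degrees of freedom stays at 4.7-5.3%.

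**Step 4: what respecting the school costs.** With 51 evaluable per group, the standard error of the risk difference without clustering is √[(0.16 + 0.25)/51] = 0.0897.

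- Individual-level 95% half-width: 1.96 × 0.0897 = 0.176.
- School-level, ICC 0: 4.303 × 0.0897 = 0.386. Ratio 0.386/0.176 = 2.2.
- School-level, ICC 0.05: 4.303 × 0.0897 × 1.492 = 0.58. Ratio 0.58/0.176 = 3.3.

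Power for 20% versus 50% comes from the noncentral t distribution on 2 degrees of freedom, with noncentrality 0.30/(0.0897·√DE):

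- ICC 0: noncentrality 3.35, power about 45%.
- ICC 0.01: noncentrality 3.00, power about 39%.
- ICC 0.05: noncentrality 2.24, power about 26%.

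Simulation with 26 per school gives 46%, 40% and 27%.

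**The case against.** The strongest reply is that this is a journal article. It does not say whether the model is marginal or mixed, its list of prognostic factors is open-ended, and a fuller plan could add a school effect. Part of that stands: the text shows that the stated model names no school term, not that the executed model had none, and a reader should not infer the latter. The reply does not remove the point. The article specifies the model, its one source of dependence, its covariates and its retention rule, and omits the randomised unit. The sample size makes the same omission.

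Other limits are fair:

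- A reader might infer that the error rate certainly exceeds 5%. It does so only if the ICC is above 0. No ICC is given, and at ICC 0 the test is close to nominal.
- A reader might picture every student trained in a school group by that school's own physiotherapist. That describes the active arm only. Sources of clustering may differ by arm, and a single assumed ICC does not reflect this.
- The calculations use one unadjusted 12-month comparison, not the planned repeated-measures model. More visits or patient-level covariates do not by themselves put between-school variance into the standard error, but the exact figures could shift.
- A reader might extend the error to KOOS, EQ5D and the sEMG sub-study. The article states no between-group model for these, so nothing there is shown to be wrong.

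**Conclusion.** The point holds in conditional form. As written, the primary analysis accounts for repeated measurements within a student and not for the school, and the sample size shares the omission. For any positive ICC the standard errors are too small and the type I error is above 5%: about 6.5% at an assumed ICC of 0.005, rising to 29-31% at 0.10. The direction does not depend on the assumed value; the size does. Because the model produces the trial's main p-value and interval, this needs correcting before analysis. Correcting it exposes a design limit that no wording can cure: four schools leave 2 degrees of freedom, and the stated 90% power is not attainable under the article's own recovery rates.

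**What to change.** State a primary inference that respects the school. Either compare school-level 12-month recovery proportions, covariate-adjusted if wished, using a t reference on 2 degrees of freedom, or fit a model with a school effect and an equivalent small-sample reference. Do not rely on an uncorrected sandwich variance with four clusters. Keep the individual-level logistic regression as supportive, labelled as conditional on these four schools and their therapists, and say openly that therapist cannot be separated from arm.

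Replace the 90% power statement with figures that reflect four schools, the assumed ICC and the chosen test, using the range worked out above or a justified ICC. As advice, apply the same principle to any between-group test of secondary and sub-study outcomes.

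The programming and wording are minor. The substantive cost is a much wider interval and power below 50%, which should be disclosed and not avoided by keeping a test that ignores the randomised unit.

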There are a number of different treatment options for PFPS. Exercise therapy has been advocated as one of the cornerstones in rehabilitation of patients with PFPS. In the short term, exercise therapy appears to have a better effect than patient education consisting of written information and general advice on exercise [11] or compared with placebo treatment [12]. But the long-term effect of exercise therapy compared with patient education or flat insoles is conflicting. After 12 months of treatment, Collins et al. found no difference in pain or function between patients receiving multimodal physiotherapy (consisting of patellofemoral joint mobilisation, patellar taping, quadriceps muscle retraining, and education) or flat insoles [13]. Contrary to these results, van Linschoten et al. found a significant effect of supervised exercise therapy compared with patient education on self-reported pain levels after 12 months, but there was no positive effect on self-reported function or self-perceived recovery [11].

One possibility to improve short- and long-term outcomes is to initiate treatment early in the clinical course. Predictors of long-term outcome (> 52 weeks) indicate that a long symptom duration [14,15], higher age [16] and greater pain severity at baseline [14] are associated with poorer outcome. These prognostic factors suggest that an early initiation of treatment among adolescents may lead to a better long-term prognosis. The purpose of this study is to examine the short- and long-term effectiveness of patient education compared with patient education and multimodal physiotherapy applied at a very early stage of the condition among adolescents. We hypothesise a significantly larger proportion of completely recovered students at the 12 months follow-up in the patient education combined with multimodal physiotherapy treatment option compared with patient education alone.

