### Sample size

From the study done by Moelgaard et al [4], we expect that at least 6% of the students will be diagnosed with PFPS. This corresponds to at least 150 students with PFPS among the 2500 students.

Based on the study done by van Linschoten et al [11] and Clark et al [27] we expect a 30% difference between intervention groups in the two categories "recovered" and "not recovered". We expect a 20% recovery in the patient education group, and 50% recovery in the group receiving patient education combined with multimodal physiotherapy. Sample size calculations show that at least 51 subjects in each group are needed to detect a statistical difference (power 0.90, alpha 0.05). To account for a drop-out rate of 10%, a minimum of 56 patients is included in each group.

The sample-size of 60 students (2 × 30 students) in the sub-study is based on the complexity of the sEMG-signal from VM during semi-squatting. Based on pilot data, 25 students are needed in each group to detect a 15% difference (0.104 vs. 0.120 Sample Entropy, standard deviation of 0.02, 80% power) between groups at three-months follow-up. To account for loss to follow-up, we increase the sample size to 2 × 30.

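### The primary outcome is recovery at 12 months, but the repeated-measures logistic regression named for it is not tied to the 12-month comparison

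*Protocol article*

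**What the plan says.** - **Outcome.** The section on self-reported outcomes fixes one time point: "The primary outcome measure is perception of recovery after 12 months measured on a 7-point Likert scale". The scale is then split into recovered and not recovered.
- **Hypothesis.** The Background section points to the same visit: "We hypothesise a significantly larger proportion of completely recovered students at the 12 months follow-up".
- **Sample size.** It is a single comparison of two proportions: "We expect a 20% recovery in the patient education group, and 50% recovery in the group receiving patient education combined with multimodal physiotherapy". No repeated measurements enter the calculation.
- **Schedule.** "Self-reported questionnaires are filled out by the students with PFPS at baseline, 3, 6, 12 and 24 months after inclusion in the study".
- **Analysis.** The groups are compared on the primary outcome by "logistic regression for repeated measurement coded as" recovered or not recovered. Adjustment for baseline values and prognostic factors is kept only if the estimate moves by more than 10%. The one interaction mentioned is treatment by compliance, as a secondary analysis.
- **Timing.** "All RCT analyses take place after the 12 months follow-up and no intermediate analyses are performed". The 3-, 6- and 12-month data would therefore be at hand. Whether the 24-month data enter is not said.

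**The concern.** A repeated-measures model uses several visits, while the primary question concerns one. The two agree only if the model lets the treatment effect differ by visit and the 12-month effect is singled out. The Statistical analysis section does neither explicitly. Its 10% rule needs one designated estimate, but a treatment-by-visit model gives one estimate per visit and the section does not say which governs.

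The time pattern matters in this trial. The Background section says "In the short term, exercise therapy appears to have a better effect than patient education", and calls the long-term evidence conflicting. It also reports that the earlier trial of supervised exercise against patient education found no benefit on self-perceived recovery at 12 months, and the Limitations section says the recovery scale was used in that same trial. The supervised programme lasts three months, so the 3-month visit falls at its end. If an effect fades, an averaged odds ratio could be reported as a 12-month result that does not exist. If an effect builds late, the average would dilute it.

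**Working it through.** **1. The plan's own figure.** Inputs from the Sample size section: 20% against 50%, power 0.90, alpha 0.05 (two-sided assumed).

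- Pooled formula: n = [1.960·√(2·0.35·0.65) + 1.282·√(0.2·0.8 + 0.5·0.5)]² / 0.30² = (1.322 + 0.821)² / 0.09 ≈ 51.0, which rounds up to 52.
- Arcsine formula: n = 2·(1.960 + 1.282)² / 0.6435² = 50.7, which rounds up to 51.
- Power at 51 per group is 0.900.

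The stated 51 therefore reproduces as a comparison at one time point.

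**2. What a common effect would estimate.** Let p̄ be the mean recovery proportion over the visits included. A common-effect odds ratio is then roughly [p̄T/(1−p̄T)] / [p̄C/(1−p̄C)].

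- Fading effect, control 20/20/20% and physiotherapy 50/35/20% at 3/6/12 months: p̄C = 20%, p̄T = 35%, so OR ≈ (0.35/0.65)/(0.20/0.80) = 2.15. The 12-month OR is 1.00.
- Late effect, control 20/20/20% and physiotherapy 20/35/50%: the averaged OR is again 2.15. The 12-month OR is (0.50/0.50)/(0.20/0.80) = 4.00.

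The same averaged odds ratio arises from no effect at 12 months and from the full planned effect.

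**3. Rejection rates by simulation.** The trajectories and within-student correlations are assumptions, not figures from the article, and school clustering is left out.

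- Set A: 56 per arm, 4,000 trials, latent correlation 0.5.
- Set B: 51 per arm, 2,000 trials, latent correlation 0.3 and 0.6, visit as a factor.
- Both use robust standard errors and compare one common effect with the 12-month contrast.

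| Pattern (set) | Control % | Physiotherapy % | Common effect rejects | 12-month contrast rejects |
|---|---|---|---|---|
| Fades to nothing (A) | 10/15/20 | 35/30/20 | 66% (OR about 2.3) | 4% |
| Fades to nothing (B) | 20/20/20 | 50/35/20 | 62-73% (OR about 2.2) | 4% |
| Milder fade to nothing (B) | 20/25/30 | 40/35/30 | 31-37% | about 5% |
| Fade, 24 months added (B) | 20/20/20/20 | 50/35/20/20 | 44-59% | 4% |
| Partial fade (A) | 10/15/20 | 40/35/25 | 89% | 8% |
| Late effect (A) | 10/15/20 | 12/30/50 | 81% | 93% |
| Late effect (B) | 20/20/20 | 20/35/50 | 60-74% | 90-91% |
| Constant effect (B) | 20/20/20 | 50/50/50 | 99-100% | 90% |
| No effect at any visit (B) | 20/20/20 | 20/20/20 | about 5% | about 5% |

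The 12-month contrast keeps its planned 90% power at 51 per group. The common-effect test does better only when the effect is constant over time.

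**The case against.** A reader might infer that the plan, as written, tests a time-averaged odds ratio. The article does not support that. It names a class of model and is silent on time terms, and a model with treatment-by-visit terms fits the same description and yields a valid 12-month contrast. The singular estimate in the 10% rule could be that contrast. The missing visit term proves little, because the sentence lists prognostic adjustments, and visit is a structural term of the model. The analysis is also stated to be of the primary outcome, which is defined at 12 months. All of this stands, so the point has to be conditional.

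A reader might also infer general inflation of the false-positive rate. That is not so: with no effect at any visit both tests reject in about 5%. The risk is that a real early effect is reported as a 12-month effect.

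It is fair, too, that the evidence of fading comes from earlier studies, while this trial hypothesises a 12-month benefit from early treatment. The trajectories are assumed, and the results depend strongly on them.

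The last defence is that a condensed article leaves model detail to a fuller plan. This carries less weight. The article itself chooses the primary model and the covariate rule. If only 12-month data were used, each student would contribute one record and nothing would be repeated, so the wording implies that other visits enter. The model so described does not by itself test the stated endpoint, and two materially different tests remain open.

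**Conclusion.** The concern holds in conditional form. Outcome and hypothesis are set at 12 months and the sample size is a one-time comparison, but the primary model is not tied to that visit. If it is fitted with one common treatment effect, the test is of an odds ratio averaged over visits.

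In the assumed scenarios with early benefit and none at 12 months, that test rejects in about 30-70% of trials against about 5% for the 12-month contrast. With a late effect its power is about 60-81% against 90-93%. These figures illustrate the consequence. They are not this trial's operating characteristics, since they rest on assumed trajectories and correlations and omit clustering in a four-school trial. A fuller analysis plan may already settle the matter. On the article alone it is open and should be closed before the data are analysed.

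**What to change.** Amend the Statistical analysis section to say:

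- which follow-up visits enter the model, and in particular whether 24 months does;
- that visit is a categorical factor with a treatment-by-visit interaction;
- that the primary test is the 12-month treatment contrast from this model, and that the 10% change rule is applied to that estimate;
- that contrasts at the other visits are secondary.

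This costs a sentence or two. The stated sample-size calculation is untouched: simulated power of the 12-month contrast is 0.90-0.91 at 51 per group under the late-effect pattern, before any allowance for clustering, which needs its own treatment. The downside is that no power is borrowed from other visits. If the effect were constant over time, power would be about 90% instead of the 99-100% of a common-effect test.

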### Interventions

Both intervention groups receive written information and education delivered during one-to-one sessions with a physiotherapist.

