### Compliance

Compliance with the supervised intervention is recorded as the number of times each student participates in the group training. Good compliance is defined as participation in at least 80% of the supervised group training sessions. Poor compliance is defined as participation in less than 40% of the group training sessions. Compliance in home exercises will be monitored by weekly follow-up using Short Message System (SMS). Good compliance in home training is defined as self-reported participation in at least 70% and poor compliance is defined as below 40%.

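### The predefined treatment-by-compliance interaction is not identifiable as written: compliance is defined only for physiotherapy-arm components and accrues after randomisation

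*Protocol article*

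**What the plan says.** All references are to the Methods of the protocol article.

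- **Statistical analysis.** The between-group comparison is by intention to treat. The secondary analyses are a per-protocol analysis and "a predefined subgroup analysis investigating the interaction between treatment and compliance".
- **Compliance.** Two measures are defined. For supervised training: "Compliance with the supervised intervention is recorded as the number of times each student participates in the group training". The upper cut-off, for good compliance, is 80% of sessions. At the lower end: "Poor compliance is defined as participation in less than 40% of the group training sessions". For home exercise, students report weekly by SMS; at least 70% is good and below 40% is poor.
- **Interventions.** The content common to both arms is education only: "Both intervention groups receive written information and education delivered during one-to-one sessions with a physiotherapist".
- **Information and education.** The education arm gets this content and a leaflet: "This session is expected to take approximately 30 minutes". No training sessions or home exercise programme are described for it.
- **Information and education plus multimodal physiotherapy.** Supervised training three times a week for three months, and instruction in home exercises, belong to this arm.
- **Randomisation.** Allocation, by school, follows the clinical examination and consent and precedes treatment.

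**The concern.** An interaction between treatment and a subgroup factor asks whether the treatment effect differs across levels of that factor. This requires the factor to take more than one level in both arms, and to be unaffected by allocation. Compliance as defined here meets neither condition. Education students have no sessions to attend and no home programme to report. Physiotherapy students acquire their value during the three months after allocation.

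At stake is how a prespecified secondary result would be read. Any number produced under this label would come from a comparison that randomisation does not protect. Students who attend regularly may differ in motivation, symptoms or prognosis from those who do not, so an association between attendance and recovery could be partly or wholly selection.

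**Working it through.** **Plan figures.** The plan gives no figure for this analysis. Its sample size is used only to set the scale of the check. The stated 51 per group (20% v 50% recovery, power 0.90, alpha 0.05) reproduces: the two-sided arcsine formula gives 50.7, rounded up to 51, and the pooled-variance formula gives 52.

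**Step 1: identifiability.** Let T = 1 for physiotherapy and 0 for education, and let C be compliance. The linear predictor of a logistic model with the interaction has columns 1, T, C and T×C. Suppose C equals a constant c0 for every education student. Then, for every student,

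T×C = C − c0(1 − T).

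When T = 1, both sides equal C. When T = 0, the left side is 0 and the right side is c0 − c0 = 0. The interaction column is thus an exact combination of the other three, whatever the data. A numerical check with 51 students per arm agrees:

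| Coding of compliance | Columns | Rank |
|---|---|---|
| Binary, education coded 0 | 4 | 3 |
| Binary, education coded 1 | 4 | 3 |
| Continuous, education coded 0 | 4 | 3 |
| Three levels (poor, middle, good), education at reference | 6 | 4 |

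More students would not change this. If C is instead left missing for education students, they drop out, T equals 1 throughout, and no treatment contrast remains.

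**Step 2: what can still be estimated.** Dropping the redundant column leaves 1, T and C (with C = 0 in education), which has rank 3 and can be fitted. The coefficient of C is then the association of compliance with recovery inside the physiotherapy arm. The other available contrast is compliers against the whole education arm. Neither is an interaction.

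**Step 3: size of possible selection (assumed rates, no treatment effect).** Let a share p of students be would-be compliers with recovery r1, and let the rest have recovery r0, the same in either arm. Assume p = 0.5, r1 = 0.30 and r0 = 0.10.

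- Education arm: 0.5 × 0.30 + 0.5 × 0.10 = 0.20, which equals the rate that the Sample size section expects there.
- Good compliers v education: 0.30 − 0.20 = +0.10.
- Poor compliers v education: 0.10 − 0.20 = −0.10.
- Good v poor within physiotherapy: 0.30 − 0.10 = 0.20.

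**Range.** With p = 0.5, the spurious complier contrast is r1 − 0.20. If prognosis is unrelated to attendance, r1 = 0.20 and the contrast is 0. The largest r1 compatible with 20% overall is 0.40 (with r0 = 0), giving +0.20. The smallest is 0 (with r0 = 0.40), giving −0.20. The documents do not say where in this range the trial would lie.

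**The case against.** The strongest reply is that this is one clause about a secondary analysis in a condensed article, and that an analysis plan not shown may set the model form and the handling of the education arm. That limits the consequence but does not remove the conflict. The article fixes both the compliance definition and the interaction, and an analysis plan could reconcile them only by changing one. Attendance at the education session would be a different variable from the one defined.

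Some stronger readings are tempting, and the documents do not support them:

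- **The model will fail to fit.** Rank deficiency means that one column is redundant. Compliance nested in the physiotherapy arm can be fitted. The defect lies in what the term is called and how it would be interpreted.
- **The trial will compare good compliers with all controls and report a dose effect.** The plan does not say this. It is only one of the contrasts that remain available.
- **The cut-offs are an error because they leave a middle band.** The band can be read as intermediate, attendance is recorded as a count, and nothing says that the interaction uses the categories. Taking 12 to 13 weeks, 3 × 12 = 36 and 3 × 13 = 39 sessions. The band is 15–28 sessions at 36 (40% = 14.4, 80% = 28.8) and 16–31 at 39 (15.6 and 31.2). Naming it would be tidy, but it is secondary.
- **The per-protocol analysis has the same fault.** The article does not define the per-protocol set, so this is not shown.

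It is also fair to say that the 10 points follow from assumed rates. They show how the bias arises, not its size in this trial.

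**Conclusion.** The point holds for the interaction as written. Under the protocol's own definition, compliance is undefined or constant in one arm, so a treatment-by-compliance interaction is not identifiable; because it accrues after allocation, it is also not a baseline subgroup factor. The conclusion rests on reading the Compliance section as the full definition, and the article offers no other.

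The contrasts that remain estimable are confounded by whatever drives attendance. The illustration gives a spurious +10 points against the education arm, within a range of −20 to +20 for an equal split and 20% overall recovery. A reader might infer that compliance cannot be studied at all. That goes too far: a complier-average effect can be estimated under added assumptions, but the protocol states none.

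The importance is moderate. The primary intention-to-treat comparison and the sample size are untouched.

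**What to change.** Delete the treatment-by-compliance interaction from the predefined subgroup analyses. Put in its place an exploratory, descriptive analysis, within the physiotherapy arm only, of attendance (as a count) and recovery. State that it is neither a randomised comparison nor evidence of effect modification.

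If a causal compliance estimate is wanted, specify a complier-average estimate with allocation as the instrument and three safeguards:

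- The exposure should be uptake of the whole physiotherapy package, defined in advance. Sessions attended alone will not do: home exercise and self-applied taping also follow from allocation and may affect recovery by other routes, which would violate the exclusion restriction.
- Standard errors must reflect the four randomised schools, two per arm, and not the number of students.
- The assumption that education students do not obtain equivalent care elsewhere should be stated. The Co-interventions section asks students to refrain from other treatment only during the intervention period.

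The cost is a change of wording for the main correction, with no new data. The optional causal estimate has a clear downside: with four schools its interval will be very wide.
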